## Abstract

Parkinson’s disease (PD) is a progressive and neurodegenerative disorder defined by physical symptoms such as hand disability and postural instability. To counteract the detrimental effects of PD, physical activity programs showed improvements in overall aspects of physical functioning. Therefore, this protocol will aim to evaluate the effect a of postural and fine motor skills training program in older adults with PD. PD individuals, with mild to moderate stage PD, aged between 65 to 80 years, will be voluntary selected from the Nursing Home Residences and Rehabilitation Centers. Subsequently, they will be randomly assigned to intervention group (PD) to receive a combined training program (postural control and fine motor skills exercises) or to the Control group (CON) to receive a stretching program. Before (PRE) and after (POST) a 12-week program both groups will perform wobble board (WB) and grooved pegboard (GPT) tests. Different performances between groups will be expected: (1) no significant differences between PD and CON group for WB and GPT test values before the beginning of the training intervention (PRE); (2) significantly better WB and GPT test values in PD subjects after the training intervention (POST) when compared to the base values (PRE); and (3) no significant differences in WB and GPT test values in CON subjects after the training intervention (POST) when compared to the base values (PRE). The findings of the present study protocol could be used for future studies investigating clinical populations, such as PD, and the effects of different rehabilitative interventions aiming to improve postural control and fine motor skills performances assessed by WB and GPT tests.

## 1. Introduction

Aging is defined as a natural, continuous and irreversible process that leads to both cognitive and physical decline, characterized by a reduction in coordination, loss of balance and the onset of several diseases [1], such as Parkinson disease (PD). PD is a slow-progression neurodegenerative disease with a high incidence in aged people, affecting 1% to 2% (1.1 million) of the older population above 65 years of age [2,3]. However, definitive conclusions about the etiology of PD have not been reached. It is generally considered to be a consequence of the simultaneous action of toxic and genetic agents (oxidative stress, mitochondrial abnormalities, excitotoxicity, inflammatory factors, environmental neurotoxins, genetic factors and brain aging) able to degenerate the actions of the dopamine neuron in individuals [4,5]. PD is mainly characterized by non-motor and motor symptoms. Non-motor symptoms, such as impairments in memory, communication, visuo-spatial skills, emotional difficulties, anxiety and depression, compromise cognitive abilities, emotionality and personality. Motor impairments, such as tremor disorder and postural changes, result in an increase of rate of falls and dysfunction in ambulation and the fine motor skills system [5,6], thus negatively affecting the individual’s self-care activities and quality of life [7]. Therefore, impairments in these abilities could negatively influence daily life activities and health-related quality of life over the lifespan, especially in a pathological population such as PD subjects.

The evaluation of postural control and fine motor skills provides essential information about neuromuscular and motor coordination systems, particularly when neurodegenerative diseases are involved. Regarding postural control, several assessments are employed. Reaching tests, such as the Star Excursion Balance [8] and the Y Balance tests [9], are the most used due to their reliability and validity in evaluating dynamic postural control. Nevertheless, due to the multifaceted nature of the postural control evaluations, by reflecting the complexity of this ability, new approaches are needed to accurately evaluate dynamic posture. Recently, computerized unstable platforms equipped with triaxial accelerometers, such as Wobble Boards (WBs), have been suggested to be reliable [10] in the evaluation of dynamic balance in different populations using different physical tasks, such as monopodalic or bipodalic stance [11], and with or without visual biofeedback conditions [12]. To evaluate fine motor skills, tests used different tasks such as position changes (sitting or tandem position), time to complete the trial test or the number of transferred blocks during Box and Blocks Test [13], Peg test [14] and the Nine-Hole Peg test [15]. The National Institute of Health Toolbox for the Assessment of Neurological and Behavioral Function [16] indicated the Grooved Pegboard test (GPT) as gold standard because it is able to provide essential and accurate information about manual dexterity in PD [17,18]. Measures extrapolated from postural control and fine motor skills evaluations are used in clinical or field settings to evaluate specific properties in healthy subjects or to highlight the effects of several diseases on these complex abilities and, subsequently, organize individualized training protocols and promote appropriate levels of physical activity among individuals with PD. To increase postural control and fine motor skills, several training programs have been proposed. Studies [19,20,21] showed that postural control exercise protocols, including stepping, walking and/or monopodalic, bipodalic stances, are effective to improve postural control in older individuals with PD. Additionally, fine motor skills interventions (placing beads into a bottle, writing and painting) proved to elicit fine-manual dexterity function in PD patients [22,23].

The Parkinson’s Foundation published the Parkinson’s Exercise Guidelines for People with Parkinson’s recommending, in particular, engagement in functional balance and coordination programs 2–3 days per week in 30–60 min sessions. PD subjects should perform static and dynamic exercises and multi-tasking training with daily integration, always considering safety procedures for subjects’ care [24].

Therefore, the beneficial effects of physical activity programs, in particular combined exercise programs, represent the key factor to manage PD symptoms and delay the pathological and physical decline [25,26], as well as when home confinement is required [27]. Consequently, the aim of the present protocol will be to evaluate the effect of a combined exercise program on postural and fine motor skills using a training program in older adults with PD.

## 2. Materials and Methods

### 2.1. Participants

PD subjects (mild to moderate PD), aged between 65 to 80 years, will be voluntarily selected from Nursing Home Residences and Rehabilitation Centers located in the regional area.

Subjects will be only recruited after medical clearance to exercise, approved by their medical practitioner [28]. The project will be carried-out and presented in the above-mentioned location through a meeting where a detailed explanation of the experimental procedures will be given. Before starting the testing sessions, informed consent from participants or their guardians will be obtained. Subsequently, the Mini Mental State Examination Test Questionnaire for PD [29] will be administered to assess the degree of pathology deterioration. The questionnaire includes seven ordered subsections (orientation, visual registration, attention/mental control, two-set verbal fluency, verbal recall, shifting and concept processing) with a total score of 30 (25–30 normal; 18–24 mild to moderate; <18 severe).

Subjects will be excluded if they: (a) have a score > 3 on the Hoehn and Yahr (H&Y) scale [30]; (b) have visual or musculoskeletal deficits; (c) have dementia or psychiatric abnormalities; (d) participate in any other medical or exercise interventions (additional to the usual received therapeutic treatment) during the study period; (e) be unable to carry out our motor performance tests independently and (f) have a Mini-Mental State Examination for PD score between 25–30 (normal) or <18 points (severe).

### 2.2. Procedures

#### 2.2.1. Preliminary Evaluations

One week before the testing session, subjects’ characteristics will be assessed. Body mass and height will be measured by means of a scale with integrated stadiometer with a precision of 0.1 kg and 0.1 cm (Seca, model 709, Vogel & Halke, Hamburg, Germany), and body mass index (BMI) will be calculated [31]. Waist circumference will be measured at the narrowest part of the abdominal region (if the narrowest part of the abdominal region is not clearly distinguishable, the waist will be measured midway between the 10th rib and the crest of the pelvic bone); hip circumference will be measured horizontally at the most protruding points in back of the gluteal region, side and front. Waist to hip ratio (WHR) will be calculated.

Subsequently, subjects will be recruited for the single-blind study and randomly allocated in two groups: PD group and Control group (CON group). PD group will participate in the combined training program; CON group will participate in a stretching program. Before (PRE) and after (POST) the combined training program (intervention) both groups will perform the tests (described in Section 2.2.3) in a randomized order. Participants in both groups will be instructed to continue with their usual care and advised not to change their daily activities during the trial. All the assessments will be carried out when participants will be in the ‘‘on’’ phase (i.e., when medications will be working and symptoms controlled).

Subjects will be able to withdraw from the study at any time for any reason without any consequences.

#### 2.2.2. Sample Size

For the calculation of sample size, no a priori hypothesis was established due the lack of previous data regarding combined exercise program (postural control and fine moto skills) in subjects with PD. For this reason, a pilot study will be performed to estimate the effect size (ES) of the intervention. The pilot study’s recruitment goal will be 15 subjects with PD for each group. Therefore, the ES, using Cohen’s d, based on the results of the pilot study, will be determined. In line with similar research, an ES value less than 0.2 will considered trivial, from 0.2 to 0.5 small, greater than 0.5 to 0.8 moderate and greater than 0.8 large [32].

#### 2.2.3. PRE and POST Evaluations

During this phase, all the subjects will perform a period of free practice with tests (WB and GPT) and procedures. The following test will be administered:-Wobble Board

The platform is composed of a wooden circular table (diameter 40 cm, height 2 cm) placed on a hemispherical plastic support (diameter 28 cm, height 6 cm) and equipped with a USB connection cable. Connecting the board to a computer, it will be possible, through a proprietary software, to visualize six concentric circles and a yellow motion marker (MM) displayed in relation to the board tilt grade. The trial countdown, as well as the time spent into target zone (TZ), will be showed on the software screen. The TZ will be indicated by a red circle showing the 0° (±1°) tilt angle measured by the triaxial accelerometer. The evaluation will be performed for both lower and upper limbs.

The aim will be to keep the MM within the TZ for as long as possible during the recording period. The upper limbs’ test session will consist of a 3-min familiarization on the WB (1 min sitting recovery) followed by three 15-s trials (right and left leg) with 1-min sitting recovery in between. During the test, the TZ will display different motion patterns: clockwise, counterclockwise, antero-posterior, medial-lateral. The lower limbs’ test session will consist of a 3-min familiarization on the WB (1 min sitting recovery) followed by three attempts of 30 s per foot with one minute of rest in between [10]. During lower limb tests, subjects will be required to be in a seated position on a chair with back support with the hands resting on their legs and WB placed in front of the chair (Figure 1).

During upper limb tests, subjects will be in a seated position, with the tested limb placed at 90° on the WB and the contralateral one (limb not performing the test) resting on the lower limb of the same side. The WB will be placed on a table and the monitor at eye level (Figure 2).

The starting limb and the order of conditions will be randomly chosen.

The test trials will be stopped and repeated if the subjects: (1) use the arms for support; (2) brace the raised leg against the contralateral leg; and (3) drop off the WB.

-Grooved Pegboard Test

The GPT (Lafayette Instrument, Lafayette, IN, USA; model 32025) is equipped with a square pegboard (10 cm × 10 cm) with 25 holes arranged in a 5 by 5 configuration, with random keyhole orientation and green steel pegs (diameter = 0.4 cm; model 32104) with a key along one side, located in a spherical tray above the keyholes. After the description of the testing procedures, the subjects will familiarize themselves with the task by filling only the first top row. Subsequently, subjects will be instructed to insert pegs one by one into the pegboard, as fast as possible, completing the rows from left to right for the right limb and from right to left for the left limb, from top to bottom (with 1-min recovery in between). Subjects will be free to perform trials when they prefer [33]. Only the dominant hand will be assessed, and all individuals with PD will perform the GPT two times. The recording time will start when subjects take the first peg and will stop when the last peg is inserted. The time to complete the GPT trials will be recorded by the operator using a digital stopwatch [18]. Lastly, if a peg falls, subjects will have to leave it and continue the test. The GPT will be placed on a table and subjects will be in a comfortable sitting position, with the contralateral limb (limb not performing the test) resting on the table (Figure 3).

#### 2.2.4. Intervention

For 12 weeks, the PD group will receive at least one 60-min session twice a week of a supervised combined training program performed in the participating facilities. The PD group will perform a combined training program (balance and fine motor skills exercises), while the CON group will perform a stretching program. The stretching program will be adopted because of its positive applications in social and emotional aspects, in integrating real tasks from daily life activities and in improving overall physical aspects such as tremor, rigidity, bradykinesia, balance and motor coordination impairments, characterizing PD disease [34].

-PD group

The exercise sessions will include a 10-min warm-up and a cool-down of 5-min of walking, joint mobility (for upper and lower limbs) exercises in clockwise and counterclockwise circling and breathing exercises and followed by 45 min postural control training. After each exercise, subjects will perform a 1-min break in a comfortable seated position.

For postural control training, progression during the intervention period will be reached. For example, visual information will be trained by closing the eyes or looking up, down and sideward; proprioceptive system will be elicited using different unstable surfaces with respect to stable platforms and vestibular system will be disturbed using music or inhibited with appropriate earphones to isolate subjects from the external setting.

Postural control exercises: bipodalic and monopodalic position (3 sets for 30-s (for limb)); stand up on the feet’ sole (10 repetitions, 3 sets); stand up on heels (10 repetitions, 3 sets); calf raises (10 repetitions, 3 sets); hip abduction (12 repetitions, 3 sets); get up and sit down from a chair (5 repetitions); walking with stop (5 min); walking with change of direction (5 min); walking on a stable surfaces (5 min); walking on an unstable surfaces (5 min); walking with a tennis ball in hands (5 min) and walking and crossing several obstacles (5 min).Fine motor skills exercises for lower limbs: in sitting position, lift legs forward by placing a tennis ball between the feet trying not to let it fall (10 repetitions, 3 sets); sitting position and barefoot, grab and drop a towel with toes (for limb) (10 repetitions, 3 sets); pass a tennis ball from foot to foot (20 steps); and in sitting position and barefoot, play a musical carpet (5 min) and toe raises with an elastic band (10 repetitions, 3 sets (for limb)).Fine motor skills for upper limbs: paper folding (5 repetitions, 3 sets); play a musical carpet (3 min); create shapes with paper (5 min); finger painting (5 min); trace a drawing (3 min); make bracelets (5 min); count coins and put in a moneybox; close a bottle (10 repetitions, 3 sets); press stamp on paper (10 repetitions, 3 sets); make letters from plasticine (3 min); and press shaped blocks on plasticine (3 min).

-CON group

The exercise programs will include stretching exercises, as follows:Stretching during seated position: straight arm forward rotation; straight arm backward rotation; straight arm up and down flapping; straight arm horizontal abduction and adduction; trunk rotation and hold. During standing position (with hands rest on chair back): hamstring stretch; calf stretch; upper trapezius stretch; straight leg forward kick; straight leg backward kick; straight leg hip adduction and abduction; and alternate knee raise (30-s, 2 cycles with 20 s rest in between) [35].

#### 2.2.5. Work Environment and Safety of Procedures

The project will be conducted in the selected Nursing Home Residences and Rehabilitation Centers. To ensure adequate safety standards, the setting designated for the protocol will be equipped with a first aid kit and a semiautomatic defibrillator. Given the progressive cognitive and physical function decline of PD, a neurologist will supervise the study protocol and during each test session, and physical exercise experts will take care of the subjects’ due precautions, such as soft surfaces, harnesses and various aids, to ensure the safety of each PD individual. Moreover, preventive measures will be taken to prevent the risk of Coronavirus disease 2019 (COVID-19) transmission. The designed setting will be periodically sanitized, and testing surfaces will be cleaned with alcohol-based disinfectants before and after each use. Lastly, the use of masks (FFP2) and gloves by the specialists will be mandatory.

#### 2.2.6. Statistical Analysis

To ensure confidentiality and protection of personal data, subjects’ data will be de-identified indicating a numerical code for each participant.

The ‘Intervention’ will be considered as an independent variable, whereas WB and GPT will be considered as dependent variables. The collected data for the analysis of WB and GPT will be expressed in time in seconds (s). Means and SDs will be calculated for each variable. The normal distribution of data will be assessed by the Shapiro–Wilk test. If data are normally distributed, parametric statistical analysis (Analysis of Variance (ANOVA) for repeated measures) will be performed. If data are not normally distributed, non-parametric statistical analysis (Kruskal–Wallis ANOVA for ranked data) will be performed. Therefore, the appropriate analysis will be used to test for differences between PD and CON groups over time (PRE and POST).

In line with previous research, statistical significance will be set at a level of *p* < 0.05. The data will be analyzed using STATA 15 (StataCorp LP, College Station, TX, USA). In addition, the intervention will be considered effective if the evaluated variables (WB and GPT) show improvements in the PD group compared to the CON one.

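### Section 2.2.6: a linear model of POST on group and PRE would usually compare the randomised groups more precisely than the planned repeated-measures ANOVA, using data already collected

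*Protocol article*

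**What the plan says.** Section 2.2.1 of the protocol article has participants "randomly allocated in two groups: PD group and Control group (CON group", and both groups take the wobble board (WB) and grooved pegboard (GPT) tests at PRE and at POST.

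Section 2.2.6 chooses the analysis by a Shapiro–Wilk test. If normality is accepted, "parametric statistical analysis (Analysis of Variance (ANOVA) for repeated measures) will be performed"; if not, "non-parametric statistical analysis (Kruskal–Wallis ANOVA for ranked data) will be performed". The chosen method is to "test for differences between PD and CON groups over time (PRE and POST" time points. The intervention counts as effective if the tests "show improvements in the PD group compared to the CON one", and "statistical significance will be set at a level of *p* < 0.05". The section does not mention PRE as a covariate.

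The only size given is in Section 2.2.2: the pilot's "recruitment goal will be 15 subjects with PD for each group". The pilot is meant to estimate Cohen's d. The article gives no power, standard deviation or PRE–POST correlation, and does not say which contrast forms the numerator of d.

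**The concern.** With exactly two time points, the group-by-time term of a repeated-measures ANOVA is the two-sample t-test on POST minus PRE. That subtracts the whole baseline value whatever the actual PRE–POST correlation. When the correlation is below 1, this subtracts too much. The estimate carries extra noise, and if the groups happen to differ at PRE, the change score over-corrects for the difference observed. ANCOVA estimates the slope from the data instead.

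What is at stake is precision. Section 2.2.2 makes an effect-size estimate the product of the pilot, so a wider interval around the group difference weakens the result the pilot exists to deliver.

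**Working it through.** **Inputs from the article.** n = 15 per group (Section 2.2.2); two randomised groups, each measured at PRE and POST (Section 2.2.1); significance level 0.05 (Section 2.2.6).

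**Assumptions.** Two-sided test; SD σ = 1 at both times; true effect 0.8 SD, one of the Cohen cut-points in Section 2.2.2; PRE–POST correlation ρ from 0.3 to 0.95, because none is given.

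There is no sample-size derivation to reproduce. The 15 per group comes without an effect size or power, and the article says that "no a priori hypothesis was established due the lack of previous data regarding combined exercise program".

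**Variance of the estimated group difference.**
- Change score (group-by-time term), 28 df: 2σ²(1 − ρ) × 2/n.
- ANCOVA, 27 df: σ²(1 − ρ²) × 2/n × [1 + 1/(2n − 4)]. The bracket is the average price of estimating the slope. At n = 15 it is 1 + 1/26 = 1.038, about 4%.
- Ratio, ANCOVA to change score: (1 + ρ)/2 × 1.038.

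**Example at ρ = 0.5.** Change score: 2 × 0.5 × 2/15 = 0.133. ANCOVA: 0.75 × 0.133 × 1.038 = 0.104. Ratio: 0.104/0.133 = 0.78.

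| ρ (assumed) | Variance ratio | Power at 0.8 SD, change score | Power at 0.8 SD, ANCOVA | Per-group n for the change score to match ANCOVA with 15 |
|---|---|---|---|---|
| 0.3 | 0.675 | 43% | 58% | 22 |
| 0.5 | 0.779 | 56% | 67% | 19 |
| 0.7 | 0.883 | 78% | 83% | 17 |
| 0.8 | 0.935 | 92% | 93% | 16 |
| 0.9 | 0.987 | 99.7% | 99.7% | 15 |
| 0.95 | 1.012 | near 100% | near 100% | 15 |

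Power is from the noncentral t distribution. The last column is 15 divided by the variance ratio, rounded.

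**Break-even.** The variances are equal when (1 + ρ)/2 = 26/27, so ρ = 0.926. Allowing also for the lost degree of freedom in the interval width, break-even is about 0.92.

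**Simulation check.** With 20,000 trials per setting at ρ = 0.3, 0.5, 0.7 and 0.9, power agreed with the formulas (56.0% and 66.9% at ρ = 0.5; 78.0% and 82.6% at ρ = 0.7). Type I error was 0.047 to 0.051 for both methods.

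**Chance imbalance at PRE.** At 15 per group the PRE difference D has standard deviation √(2/15) = 0.37 SD. Given D, the change-score estimate is off by (ρ − 1)D on average. For D = 0.37 that is −0.18 SD at ρ = 0.5 and −0.11 SD at ρ = 0.7. Averaged over randomisations the shift is zero; it matters for the particular sample drawn.

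**The non-parametric branch.** Kruskal–Wallis compares independent groups and does not model the PRE–POST pairing. Section 2.2.6 does not say which values it is applied to. Unless these are change scores, baseline information would actually be lost here.

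**The case against.** The strongest reply is that nothing here is a mistake. The group-by-time test is valid in a randomised two-group design, and the simulation bears this out. Details of covariate adjustment often sit in an analysis plan that is not shown. The gain depends on a correlation the article does not give, and vanishes near 0.9. Fifteen per group is a pilot goal with no power target, so the power figures do not show a shortfall against any stated aim.

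Most of that stands, and it sets the grade of the point. It does not remove the point: Section 2.2.6 names a specific method, and the alternative uses the same data with little downside.

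Some stronger readings are tempting but not supported:
- *The plan throws the baseline away.* The interaction test uses every PRE value, with the slope fixed at 1.
- *The planned comparison is biased.* Under randomisation it is unbiased overall; the over-correction is conditional on the imbalance observed.
- *The test might be the group main effect.* That would average PRE with POST and halve the effect (power about 23% at 0.8 SD and ρ = 0.5). But Section 2.2.6 speaks of group differences over the two time points and of improvement relative to CON, which most naturally means group-by-time.
- *The first hypothesis shows concern about baseline imbalance.* The Abstract and Discussion only list no PRE difference as an expected result.

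**Conclusion.** The point holds as a nearly free improvement in efficiency. At 15 per group, ANCOVA cuts the variance of the group comparison by about 22% at ρ = 0.5, 12% at 0.7 and 6% at 0.8. The large-sample formula (1 + ρ)/2 alone would suggest 25%, 15% and 10%, which is too generous at this size. The gain is about 1% at ρ = 0.9, and at 0.95 there is a loss of about 1%.

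The variance ratios rest on equal variances at PRE and POST and on an assumed ρ; the power figures also need the assumed 0.8 SD effect. They apply to the pilot's 15 per group, since no main-trial size is set. The conclusion does not depend on knowing ρ exactly: over the range examined, the possible loss is trivial and the possible gain is material.

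**What to change.** In Section 2.2.6, replace the repeated-measures ANOVA for each WB and GPT endpoint with a linear model of POST on group and PRE. Report the adjusted PD-minus-CON difference with its 95% confidence interval as the treatment effect. In Section 2.2.2, state that this contrast is the numerator of the effect size.

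If a non-parametric fallback is kept, use a baseline-adjusted form, for example rank ANCOVA, instead of Kruskal–Wallis on unpaired values.

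The cost is a few sentences of text, one model degree of freedom, and about 4% variance inflation at 15 per group. The gain outweighs this unless ρ exceeds about 0.92. No new data or visits are needed.

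### The fallback for non-normal data, Kruskal–Wallis on raw PRE and POST times, ignores the pairing and has no group-by-time contrast, so it does not test PD versus CON over time.

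*Protocol article*

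**What the plan says.** Section 2.2.1 of the protocol article fixes the design as two randomised arms with two measurements per participant: "Before (PRE) and after (POST) the combined training program (intervention) both groups will perform the tests".

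Section 2.2.6 takes the raw measurements as the variables: "The collected data for the analysis of WB and GPT will be expressed in time in seconds (s". It defines no change score and names intervention as the independent variable. A Shapiro–Wilk test then selects one of two methods:

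- Normal: "If data are normally distributed, parametric statistical analysis (Analysis of Variance (ANOVA) for repeated measures) will be performed".
- Not normal: "If data are not normally distributed, non-parametric statistical analysis (Kruskal–Wallis ANOVA for ranked data) will be performed".

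Both branches are meant to answer the same question: "the appropriate analysis will be used to test for differences between PD and CON groups over time (PRE and POST". The significance level is p < 0.05. The success rule is that "the intervention will be considered effective if the evaluated variables (WB and GPT) show improvements in the PD group compared to the CON one". No test or contrast is attached to that rule.

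The Discussion (Section 3) words the expected results differently: a significant PRE-to-POST change within the PD arm and none within the CON arm.

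**The concern.** Kruskal–Wallis compares independent groups on one factor. It has no within-subject term and no interaction term. Repeated-measures ANOVA has both, and its group-by-time term is the comparison the plan asks for. The two branches therefore test different hypotheses, and a normality p-value decides which one is tested.

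This is not detail left to an analysis plan. The article names a specific method, which a later document would have to contradict.

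What is at stake depends on how the test is applied. Over the four arm-by-time cells it can become significant because both arms improved together. Within each arm it ignores the pairing. On POST alone it discards the baseline.

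Some shared improvement is plausible on the article's own account. Section 2.2.4 credits the control stretching programme with benefits for balance and motor coordination, and both arms repeat the same timed tests.

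**Working it through.** **Inputs from the article.** Two arms, each measured at PRE and POST (Section 2.2.1); significance level 0.05 (Section 2.2.6); 15 per arm, the pilot recruitment goal (Section 2.2.2). The article states no power or error rate for this analysis, so there is no figure to reproduce.

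**Assumptions, none given in the article.** PRE–POST correlation r = 0.7, with 0.5 and 0.9 as a range; a time shift common to both arms of 0, 0.5, 0.8 or 1.0 SD; no dropout; one outcome at a time.

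**Method.** At least 20,000 simulated trials per setting. Kruskal–Wallis uses ranks only, so its results on raw values are the same for normal and log-normal data apart from simulation error. Separate runs agree to within about one percentage point for the four-cell test.

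**Step 1. No treatment effect, r = 0.7. Percentage of trials with p < 0.05, or showing the pattern named:**

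| Common shift (SD) | Kruskal–Wallis, four cells | Within-arm Kruskal–Wallis: PD significant, CON not | Kruskal–Wallis, POST only | Kruskal–Wallis on change | Repeated-measures interaction |
|---|---|---|---|---|---|
| 0 | 4 | 0.2 | 5 | 5 | 5 |
| 0.5 | 22 | 13 | 5 | 5 | 5 |
| 0.8 | 74 | 24 | 5 | 5 | 5 |
| 1.0 | 96 | 13 | 5 | 5 | 5 |

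Over r = 0.5 to 0.9 with log-normal data, the four-cell rates are 3.8–4.5%, 19–25%, 72–80% and 93–98% for the same shifts. The result does not hinge on one correlation. It does hinge on a common shift being present.

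With no shift, the within-arm test rejects in only 0.2% of trials instead of 5%, because it does not use the correlation between a participant's two values.

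**Step 2. Power, PD alone shifting by 0.8 SD, r = 0.7:**

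- Kruskal–Wallis, four cells: 48%
- Kruskal–Wallis, POST only: 54%
- Rank-sum test on change: 76%
- Repeated-measures interaction (equal to a t-test on change): 78%
- ANCOVA of POST on arm and PRE: 83%

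The gap between POST alone and change follows from the variances. POST has variance σ²; change has variance 2σ²(1 − r). At r = 0.7 that is 2 × 0.3 = 0.6σ². At r = 0.5 it is 2 × 0.5 = 1.0σ², the same as POST, so nothing is lost there (54% against 54–57%). At r = 0.9 it is 0.2σ², and power is 54% against 99% or more.

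**Step 3. Interaction against ANCOVA.** The variance ratio is 2(1 − r)/(1 − r²) = 2/(1 + r). At r = 0.7 this is 2/1.7 = 1.18; at r = 0.5 it is 2/1.5 = 1.33. Both tests hold the 5% level, so this is a matter of efficiency only.

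**Step 4. Link to the verdict.** If a significant four-cell result must also come with PD significantly better than CON at POST, wrong positives fall to about 2–3% at common shifts of 0.8 and 1.0 SD.

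**The case against.** The strongest reply is that Kruskal–Wallis is not unusable in this design. Applied to each participant's POST-minus-PRE change, it is the rank-sum test for two arms. It keeps about 5% error under any common shift and has about 76% power at r = 0.7. A reader might infer that the named test can never answer the question, and the calculation does not support that. What stands is that the article defines its variables as times in seconds and mentions no change score. As written, the valid use is not the one specified.

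Second, a reader might take the 74% and 96% as the trial's chance of wrongly declaring success. The article does not support that either. It does not say the test runs over four cells, and its success rule requires PD to improve compared with CON, which a shared improvement does not meet. On one reasonable reading of that rule, wrong positives are about 2–3%. On the within-arm reading suggested by the Discussion, they reach about 24%. Because no test is tied to the rule, neither reading can be excluded.

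Third, the shifts and the correlation are assumed, and Section 2.2.3 includes familiarisation, which may reduce practice effects. This stands, and it is why the zero-shift row is shown.

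Fourth, how often the branch would be used is unknown. For a single sample of 15 log-normal values, Shapiro–Wilk flags 11%, 16% or 38% at an assumed log-SD of 0.2, 0.3 or 0.5. Testing several cells would raise this. Wobble-board time in the target zone is also capped by the 15-s and 30-s trials, which was not simulated. The plan provides for the branch, so it should be right.

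**Conclusion.** The concern holds in limited form. On raw PRE and POST times, the fallback treats paired values as independent and has no group-by-time contrast, so it does not test PD versus CON over time. Depending on how it is applied, it responds to a time effect shared by both arms or loses power.

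The sizes rest on 15 per arm, r = 0.7 and the assumed shifts. They describe the test, not the final verdict. They also apply to the pilot size; Section 2.2.2 gives no size for a later trial.

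The parametric branch is not at fault: the repeated-measures interaction is a valid test of the stated question, and preferring ANCOVA is only a gain in efficiency.

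**What to change.** In Section 2.2.6, name the between-arm difference in PRE-to-POST change as the deciding contrast in both branches, and tie the success rule to it.

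- Normal branch: state that the group-by-time interaction is the test that decides.
- Non-normal branch: replace Kruskal–Wallis on raw values with a rank-sum (Mann–Whitney) test on POST-minus-PRE change, or with a rank or permutation ANCOVA of POST adjusted for PRE.
- Describe the within-arm PRE-to-POST results expected in the Discussion as descriptive, not as the basis for the verdict.
- Optional, for efficiency: use ANCOVA of POST on arm and PRE in place of the repeated-measures interaction.

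The cost is a few sentences. PRE is already collected, so no new data, visits or participants are needed.
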